### Analysis methods

2.6

Bayesian analysis methods will be used for all objectives.

For the primary safety objective, the null hypothesis is that the 6‐month freedom from major RV lead‐related complications is equal to or below 90%. For the safety objective to be successfully met, the 95% two‐sided credible interval for the 6‐month RV lead‐related major complication rate must have a lower bound exceeding 90%.

The primary safety objective addresses the entire safety profile of the LEADR ICD lead as fractures are included in major complications. The determination of the pre‐specified performance goal of 90% for the lead‐related major complication endpoint aligns with previous ICD and CRT‐D studies: Block HF, Reverse, Evera MRI, and PainFREE SST.^22^, ^23^, ^24^, ^25^ An assessment of comparable major complication‐free rates at 6 months for transvenous devices showed observed rates as low as 95.7% (Figure S2).

For the primary safety objective, all patients undergoing an implant attempt of the LEADR ICD lead will be included in the analysis. The objective will be analyzed using a time‐to‐event analysis. The time to event will be defined as a subject's time to first LEADR ICD lead‐related major complication. In the case of no event, patients will be censored at the time point of their last exposure to the LEADR ICD lead.

For inferential analyses, a piecewise exponential model will be assumed with two intervals of interest: 0‐1‐month post‐implant, and 1 month and beyond post‐implant, as it is possible the rate of lead‐related major complications may differ in the acute (first 30 days) compared to more chronic time points (Figure S2).

Bayesian Prior Gamma distributions will be combined with the prospective event/follow‐up data to generate posterior distributions for each event rate. These posterior distributions will be used to construct the 95% two‐sided credible interval for the freedom from major complication at 6‐months as described above. Further details about the specification of the Bayesian priors can be found in the supplementary methods.

For the primary efficacy objective, the null hypothesis is that the implant defibrillation success rate is equal to or below 88%. For the objective to be successfully met, the 95% two‐sided credible interval must have a lower bound that exceeds 88%. The analysis cohort will be defined as patients who complete the implant defibrillation testing protocol.

Defibrillation implant success for transvenous devices, though no longer routinely performed, has historically been shown to be as low as 88%.^26^ The threshold of 88% has also been used in pivotal trials for alternative defibrillation devices (subcutaneous ICD^27^ and extravascular ICD^28^), demonstrating a precedent for a performance goal of 88%.

The primary efficacy objective will be analyzed using a Beta‐Binomial Bayesian model as described above in the sample size section from which a 95% two‐sided credible interval for defibrillation success will be constructed. Details can be found in the supplementary methods.

For the secondary objective analyses, time‐to‐event analyses will be performed. Time to event will be set as the interval from the time of implant to the time of the first LEADR ICD lead fracture. Patients without fractures during the time period of interest will be censored at their time point of last exposure to the LEADR ICD lead. All patients undergoing an implant attempt of the LEADR ICD lead will be included in the analysis. More information about the analysis for the secondary objective can be found in the supplementary information.

For the secondary objective analyses, time‐to‐event analyses will be performed. Time to event will be set as the interval from the time of implant to the time of first LEADR ICD lead fracture. Patients without fractures during the time period of interest will be censored at their time point of last exposure to the LEADR ICD lead. All patients undergoing an implant attempt of the LEADR ICD lead will be included in the analysis. More information about the analysis for the secondary objective can be found in the supplementary information.

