### Objectives and study endpoints

1.3

The LEADR study has two primary objectives. The primary safety objective is to demonstrate that the freedom from major complications related to the LEADR ICD lead at 6 months post‐implant exceeds a pre‐specified threshold of 90%. The endpoint is defined as a subject's first occurrence of a major complication related to the LEADR ICD lead, as determined by an independent Clinical Events Committee (CEC), that occurs on or before 6 months (182 days) post‐implant. Major complications are those complications resulting in death, lead fracture, hospitalization, prolongation of an existing hospitalization by at least 48 h, and/or system revision (reposition, replacement, explant). The primary efficacy objective is to demonstrate that defibrillation efficacy exceeds a threshold of 88% in a subset of patients. The defibrillation endpoint will be met if a single 18 Joule shock terminates an induced sustained shockable ventricular arrhythmia (SSVA) or if two consecutive induced SSVAs are terminated with 25 J shocks (Figure 2).

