For analyzing the primary safety objective, a piecewise exponential survival model employing Gamma priors which yield a skeptical prior distribution for a 6‐month freedom rate (median of 56.2%) is used. The posterior distribution will be computed using the conjugate distribution for the Gamma priors. Information about simulations to study the statistical operating characteristics of the adaptive design and details about sample size calculations for the primary efficacy objective can be found in the supplementary information.

Several simulation studies using the statistical programming language R v4.0.2 (r-project.org) were performed to study the statistical operating characteristics of the adaptive design. For all simulations, an attrition rate of 4% at 1 month and 10% 1‐year post‐implant were assumed. Power for the primary safety objective was estimated by assuming a major complication‐free rate of 95.5% and 94.5% at 1 and 6 months, respectively. Simulation results showed that the adaptive study design has good frequentist operating characteristics, such as power >90% and Type I error <2.5% for the primary safety objective (Table S1).

Additionally, simulations were carried out under two different scenarios for the secondary objective to assess ensure the adaptive design could differentiate between a high‐performing and low‐performing lead. Specifically (1) a high‐performing scenario where the LEADR ICD lead has an expected fracture‐free rate of 99.9% at 12 months, and (2) a poor‐performing scenario where the lead has a 98.4% fracture‐free rate at 12 months. In the high‐performance scenario, there is a 94% chance of observing 1 or fewer fractures within 6 months after the 500th implant attempt, compared to 1.4% chance for the poor‐performing scenario.

The primary efficacy objective will be analyzed using a Beta‐Binomial Bayesian model with a skeptical Beta before ensure good Frequentist operating characteristics. To determine the sample size for the primary efficacy objective, a defibrillation success rate of 97% was assumed to study statistical power. To assess the Type I error, a success rate of 88% was assumed. Simulation studies determined that at least 95 patients completing the defibrillation testing protocol will provide a power >90% with a Type I error <2.5%.

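### The primary safety success criterion names the complication rate where it means freedom from complications: a wording error in the decision rule, not a design flaw

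*Protocol article*

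**What the plan says.** Section 1.3 (Objectives and study endpoints) sets the primary safety objective as to "demonstrate that the freedom from major complications related to the LEADR ICD lead at 6 months" "post‐implant exceeds a pre‐specified threshold of 90" per cent. The endpoint is a subject's first major complication related to the LEADR ICD lead, as determined by the Clinical Events Committee, within 182 days of implant.

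Section 2.6 (Analysis methods) first states the null hypothesis: 6-month freedom from major RV lead-related complications "is equal to or below 90%. For the safety objective to be successfully met". The same sentence that opens with those last words then gives the criterion: the 95% two-sided credible interval for the 6-month RV lead-related "major complication rate must have a lower bound exceeding 90" per cent.

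Further on, section 2.6 says that the posterior distributions will be used to build the "95% two‐sided credible interval for the freedom from major complication at 6‐months as described above".

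Section 2.4 (Adaptive design and sample size) describes the prior by its median 6-month freedom rate, 56.2%. It bases power on a "major complication‐free rate of 95.5% and 94.5% at 1 and 6 months, respectively" and reports "power >90% and Type I error <2.5% for the primary safety objective".

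**The concern.** The null hypothesis and the success criterion stand in adjacent sentences and refer to opposite quantities. The null is about the proportion of patients free of a major complication; the criterion is about the proportion who have one. A lower bound above 90% on the second would mean that more than nine patients in ten had a major complication.

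This cannot be read as shorthand. The article has the correct term, a major complication-free rate, and uses it both in section 2.4 and elsewhere in section 2.6. The sentence matters because it is the only place where the article says what result meets the primary safety objective. A reader of a pivotal study should not have to override the words of the decision rule to learn what it is.

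A smaller mismatch sits in the same two sentences. They speak of RV lead-related complications, while the endpoint definition and the time-to-event definition speak of LEADR ICD lead-related ones.

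**Working it through.** **Inputs from the article**

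- Threshold 90%; 95% two-sided credible interval (sections 1.3 and 2.6).
- Assumed freedom 95.5% at 1 month and 94.5% at 6 months; stated power above 90% and Type I error below 2.5% (section 2.4).
- Attrition: "an attrition rate of 4% at 1 month and 10% 1‐year post‐implant were assumed" (section 2.4).
- Piecewise exponential model, 0–1 month and 1 month onward, with Gamma priors giving a median 6-month freedom of 56.2% (sections 2.4 and 2.6).
- Minimum of 500 implant attempts (section 2.4).

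**Assumptions**

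The Gamma parameters are in a supplement that is not at hand. Shapes of 0.1, 0.5 and 1.0 were tried, with the same shape and rate in both intervals and the rate solved to give the 56.2% median. Sample size was held at 500 without adaptation. Administrative follow-up was taken as 12 to 27 months (12 months plus a uniform 0–15 months for staggered entry).

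**How the two readings relate**

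If the interval for freedom is (L, U), the interval for the complication rate is (1 − U, 1 − L).

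- Criterion on freedom: L > 0.90, which is the same as an upper limit for the complication rate below 10%.
- Criterion as worded: 1 − U > 0.90, which is the same as an upper limit for freedom below 10%.

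**Step 1: reproduce the stated power with the criterion on freedom, by exact binomial**

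Take p0 = 0.90 and p1 = 0.945, and require the smallest number of complication-free patients that keeps the one-sided error at or below 2.5%.

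| n | Complication-free needed | Type I error | Power |
|---|---|---|---|
| 500 | 464 | 1.9% | 95.7% |
| 480 | 445 | 2.5% | 96.1% |
| 450 | 418 | 2.1% | 94.1% |

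The stated power above 90% is reproduced.

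**Step 2: score both readings in the planned model**

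Monthly hazards follow from the planning rates, with 182 days = 5.98 months:

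- first month: −ln(0.955) / 1 = 0.0460
- thereafter: −ln(0.945 / 0.955) / 4.98 = 0.0105 / 4.98 = 0.0021

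Each row is 4,000 simulated trials of 500 patients with the article's attrition.

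| Gamma shape | Mean interval, complication rate | Success, criterion on freedom | Success, criterion as worded |
|---|---|---|---|
| 0.1 | 3.8% to 7.5% | 98.8% | 0 |
| 0.5 | 3.9% to 7.6% | 97.7% | 0 |
| 1.0 | 4.0% to 7.7% | 97.8% | 0 |

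On the freedom scale these intervals run from about 92.3–92.5% to 96.0–96.2%, clear of 90%. On the complication scale the true value is 1 − 0.945 = 5.5%, and the largest lower limit in any of these trials was about 7.7%. That is far too low for any plausible prior to lift it to 90%.

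**Step 3: check the direction of the wording**

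With an assumed 95% complication rate at 6 months (80% by 1 month), the criterion as worded was met in all 1,000 simulated trials, and the criterion on freedom in none. This run used an illustrative Gamma prior (shape 0.5, rate 1) not matched to the 56.2% median. It shows only which way the sentence points.

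**The case against.** The strongest reply is that the article resolves the slip itself. The later sentence in section 2.6 says that the interval is built for freedom from major complication and refers back to what was described above, which is the success criterion. Every other primary-safety statement tied to the 90% goal is also on the freedom scale: the objective, the null, the prior, the power assumption, and the benchmark of complication-free rates as low as 95.7%. A lower bound above 90% on a complication rate makes no sense as a safety goal, so nobody would programme it.

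This stands as an argument about consequences. A reader might infer from the sentence that a safe lead can never succeed, or that the true power is zero against a claim above 90%. The article does not support that. Those figures describe the literal words only, and the interval construction and stated power show that a different rule is meant. It does not stand as a reason to leave the sentence alone: the back-reference points to a sentence that names the other quantity, so it exposes the conflict as well as settling it.

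A reader might also infer that the RV-lead wording widens the endpoint to complications of a substitute RV lead placed after a failed LEADR attempt. The article does not support that either. Section 1.3 fixes the endpoint as related to the LEADR ICD lead. Section 2.6 defines event time by LEADR ICD lead-related complications and censors event-free patients at last exposure to that lead. No count of such patients is given, so no effect can be sized. What remains is a mismatch of terms.

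**Conclusion.** The success criterion for primary safety is wrong as worded: it names the major complication rate where the objective, null, prior, power basis and interval description all require freedom from major complications. It is a wording error in the decision rule. The intended rule can be recovered with confidence, because the stated power above 90% fits only the freedom scale (94–96% by exact binomial at n = 450–500; 97.7–98.8% by simulation at 500 patients).

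The direction of the error and the identity of the intended rule do not depend on the assumed priors. The simulated power figures do. They also rest on a fixed sample of 500 and the assumed follow-up pattern.

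One further inference should be resisted. With true freedom set at 90% (6,000 trials per prior, early and late hazards in the planned proportion), the simulated Type I error was 2.5–3.1%, with a Monte Carlo standard error of about 0.2 percentage points. Because the actual Gamma parameters are not shown and the adaptation was not modelled, this does not contradict the stated figure below 2.5%.

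**What to change.** Restate the criterion in section 2.6 as follows: the primary safety objective is met if the lower limit of the 95% two-sided credible interval for 6-month freedom from LEADR ICD lead-related major complications exceeds 90%.

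As a minor consistency edit, use LEADR ICD lead-related in place of RV lead-related in both the null hypothesis and the criterion, so that they match the endpoint definition. If the full protocol or analysis plan carries the same sentence, correct it there too.

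The cost is an edit to two adjacent sentences. Sample size, threshold, prior, model and stated operating characteristics are unchanged.

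### Primary safety: the endpoint stops at day 182, but the censoring rule and second hazard interval do not, so Type I error control depends on what happens after month 6

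*Protocol article*

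**What the plan says.** All references are to the protocol article.

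- **Endpoint (1.3, Objectives and study endpoints).** A subject's first lead-related major complication "that occurs on or before 6 months (182 days) post‐implant".
- **Hypothesis and success rule (2.6, Analysis methods).** "the null hypothesis is that the 6‐month freedom from major RV lead‐related complications is equal to or below 90"%. The 95% two-sided credible interval "must have a lower bound exceeding 90"%. I read the interval as one for freedom from complications.
- **Event time (2.6).** "The time to event will be defined as a subject's time to first LEADR ICD lead‐related major complication". This sentence has no 182-day limit.
- **Censoring (2.6).** "In the case of no event, patients will be censored at the time point of their last exposure to the LEADR ICD lead".
- **Model (2.6).** Piecewise exponential with Gamma priors and two intervals: "0‐1‐month post‐implant, and 1 month and beyond post‐implant".
- **Timing (2.4, 2.1).** In the base case the analysis falls when the first 500 implant attempts have had 12 months of opportunity for follow-up. Enrollment is expected to take about 15 months.
- **Operating characteristics (2.4).** Power above 90% at 95.5% freedom at 1 month and 94.5% at 6 months, and Type I error below 2.5%.

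**The concern.** The endpoint definition and the analysis use different time windows, and the two can be combined in two ways.

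- **Reading A.** Events are limited to day 182, as in 1.3, but exposure runs to last contact, as in 2.6. Person-time after day 182 then enlarges the denominator of the second-interval hazard with nothing added to the numerator. The months 1–6 hazard is biased down and 6-month freedom is biased up.
- **Reading B.** All first events count, whenever they occur. Events and exposure then match, but the months 1–6 hazard is correct only if the hazard is flat from month 1 to the end of follow-up. The article does not state that assumption as a condition of the error rate.

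What is at stake is the decision on the primary safety objective. Follow-up length also depends on observed fractures, which are themselves a component of this endpoint. If the hazard is not flat, the quantity called 6-month freedom therefore shifts with the adaptive path.

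**Working it through.** **1. Share of late person-time.** Follow-up at analysis runs from 12 to 12 + 15 = 27 months. With uniform accrual the mean is 12 + 15/2 = 19.5 months. Day 182 is 5.98 months. Before attrition, second-interval exposure per patient is 19.5 − 1 = 18.5 months, of which 19.5 − 5.98 = 13.52 lies after day 182. That is 13.52/18.5 = 73%. With the article's attrition (4% at 1 month, 10% at 1 year) the simulated share is about 71%. It ranges from 54% to 77% for accrual of 0 to 24 months.

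**2. How much of the 6-month rate this touches.** At the design rates the cumulative hazard is −ln 0.945 = 0.0566, of which −ln 0.955 = 0.0460 falls in month 0–1. The month 0–1 share is 0.0460/0.0566 = 81%, and it has its own parameter.

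**3. Null used.** True 6-month freedom is exactly 90%, so total hazard is −ln 0.90 = 0.1054, split in the same 81:19 proportion (the proportional null). Month 0–1 contributes 0.0858, so 1-month freedom is 91.8%. Months 1–6 contribute 0.0196.

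**4. Expected bias.** The fitted months 1–6 hazard is the truth multiplied by (early share + late share × late-hazard ratio):

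- Reading A: 0.0196 × 0.283 = 0.0055. Total 0.0913, apparent freedom 91.3%.
- Reading B, later hazard halved: 0.0196 × (0.286 + 0.5 × 0.714) = 0.0126. Total 0.0984, apparent freedom 90.6%.
- Reading B, later hazard doubled: 0.0196 × (0.294 + 2 × 0.706) = 0.0334. Total 0.1192, apparent freedom 88.8%.

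**5. Simulation.** 500 implant attempts, uniform accrual over 15 months, analysis 12 months after the last implant, and the article's attrition. The posterior for each interval is conjugate Gamma, and success means P(H1 + H2 < −ln 0.90) > 0.975. The article gives only the prior median of 6-month freedom (56.2%). I therefore assumed the same Gamma(a, b) for each interval's cumulative hazard, with b set so that the sum, Gamma(2a, b), has median −ln 0.562 = 0.576. Prior weight was varied through a = 0.1, 0.5, 1 and 2.

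The article's own figures come first (constant hazard, all events counted), then the alternatives:

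| Case | a = 0.1 | 0.5 | 1 | 2 |
|---|---|---|---|---|
| Power, open interval, constant hazard | 98.5% | 98.1% | 97.2% | 96.2% |
| Type I, Reading B, constant hazard | 2.9% | 2.3% | 2.0% | 1.4% |
| Type I, Reading B, later hazard ×0.9 | 3.6% | 3.2% | 2.5% | 1.6% |
| Type I, Reading B, ×0.8 | 4.4% | 3.7% | 3.1% | 2.1% |
| Type I, Reading B, ×0.5 | 7.7% | 6.9% | 5.7% | 4.1% |
| Type I, Reading A, constant hazard | 17.6% | 15.9% | 13.8% | 10.7% |
| Type I, cut at day 182 | 2.9% | 2.1% | 1.6% | 0.8% |
| Power, cut at day 182 | 96.9% | 95.0% | 93.9% | 90.4% |

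The stated power and Type I error are reproduced under constant hazard, except that the near-flat prior (a = 0.1) gives 2.9%. That prior gives 2.9% after the cut as well, so that excess comes from the prior and not from the time window. At a = 0.5, doubling the later hazard gives 0.2%. With 800 implants and a = 0.5, Reading B gives 2.5% at constant hazard and 8.3% at half. The fracture-driven sample-size rule itself was not simulated.

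**The case against.** The best defence is that Reading B is the natural one. Section 2.6 defines event time without a cap and censors only event-free patients, so events and exposure share one window. Under the model's own constant hazard, the claimed error rate then holds. Using all exposure to estimate a constant chronic hazard is a recognised way to gain precision. The introduction says the annual rate of lead defects rises over time, which would make the test conservative. The supplement and any SAP are not shown and may set a day-182 cut.

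Much of this stands, and it rules out three stronger inferences:

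- A reader might infer that Type I error simply exceeds 2.5%. The documents do not support that. It depends on the late hazard or on Reading A.
- A reader might infer that months 7 to 27 set the 6-month rate. They dominate only the months 1–6 part, which is 19% of the cumulative hazard at the design rates.
- A reader might produce false-pass rates of 40%, 75% or 94% by moving more of the null's hazard into months 1–6. With 1-month freedom of 95.5% and 6-month freedom of 90%, that hazard is ln(0.955/0.90)/ln(0.955/0.945) = 0.0593/0.0105 = 5.6 times the design value. Nothing in the article supports such a pattern.

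The defence does not remove the mismatch. Section 2.6 states the censoring rule and the intervals outright and, for this analysis, leaves only the prior specification to the supplement. Reading B also departs from the endpoint in 1.3. The reason given for a cut at one month, that acute and chronic rates may differ, does not show that the hazard is flat from then on.

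**Conclusion.** The point holds in a conditional form. The 182-day endpoint does not match an analysis that censors at last exposure and has an open second interval. About 71% of the information on the months 1–6 hazard comes from outside the endpoint window.

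- If late exposure counts without late events, Type I error is about 11% to 18%.
- If late events count, it is 1.4% to 2.9% under constant hazard, about 4% to 8% if the later hazard is half, and below nominal if the later hazard rises. The heaviest prior tried still tolerates a drop to 0.8 times.

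These figures rest on assumptions that the article does not settle: the prior shape (0.1 to 2), the proportional split of the null, the late-hazard ratio and uniform accrual. They do not show that the stated error rate is wrong. They show that it rests on a choice of reading and on a hazard assumption, neither of which is stated.

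**What to change.** For the primary safety analysis, censor every event-free patient at the earlier of last exposure and day 182, count only first events up to day 182, and define the second interval as ending there. Alternatively, keep all follow-up and add a cut-point at day 182 so that later data have their own hazard. With independent priors this gives the same 6-month estimate. Re-run the Type I and power simulations on that definition, and report later complications separately.

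The text change is a sentence or two, plus a re-run of existing simulations. Type I error then no longer depends on the hazard after month 6. Power falls by about 2 to 6 points depending on prior weight, to about 90% to 97%. At the heaviest prior tried it is 90.4%, only just above the stated 90%, so the re-run should use the actual Gamma parameters.

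If the sponsor prefers to keep the open interval, the plan should say that events after day 182 count, state the constant-hazard assumption, and show Type I error under falling and rising later hazards.

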### Data collection

2.2

Patients will be implanted with the LEADR ICD lead connected to a Medtronic commercially released MR conditional ICD or CRT‐D device. Any commercially released RA and LV lead may also be implanted. If a lead cannot be successfully implanted, the clinical plan will be determined by the physician. Clinical data will be collected at the study visits detailed in Table 2. At implant, chest X‐ray, fluoroscopic cine images, and analyzer/programmer printouts will be obtained. Defibrillation testing will be performed at the time of implant in enrolled patients until the sample size requirement of at least 95 completed defibrillation testing protocols has been reached. Electrical testing will include R‐wave amplitude and pacing capture threshold testing performed with decrement pacing voltage amplitude starting at 5.0 volts at a fixed pulse width of 0.4 ms. Additionally, lead impedance will be measured. All procedure or system‐related adverse events will be collected, adjudicated, and followed until resolution. For analysis, procedure‐related major complications will be reported separately from other major complications and all complications can be reported in ICD and CRT‐D patient populations separately. Subject visits will occur at enrollment, baseline, implant, pre‐hospital discharge, 3, 6, 12, 18 months post‐implant, and every 6 months thereafter until study closure (Figure 3).

**Table 2 jce15747-tbl-0002:** Data collection and study procedure requirements at subject visits

Study procedure	Enrollment/baseline	Implant	PHD	3/6/12/18 Months (in office)	Long‐term (post‐18 months, remote or in office)	Unscheduled	System modification	Study exit
Informed consent	X							
Inclusion/exclusion assessment	X							
Physical exam, demographics, cardiovascular medical history, surgical history	X							
Physician lead and catheter handling assessment		X					X^a^	
System and procedure information		X					X	
Sensing, Impedance, and pacing tests		X	X	X	X	X^b^	X	
Defibrillation testing		X^c^						
Fluoroscopy of final lead position (LAO)		X					X^a^	
Chest radiographs (AP/PA and lateral)			X				X^a^	
Save‐to‐media/save session files		X	X	X	X	X	X	X
Medications		X						
AEs (including AEs with fatal outcome), device deficiencies, study deviations, lead and systems alerts, lead systems events	As they occur							

*Note*: In‐person visits could be replaced by other options as per required per local regulations in the case of, e.g., a pandemic.

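### The completers-only efficacy cohort can drop patients because a shock failed, so defibrillation success can be biased upward and the stated Type I error is not assured

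*Protocol article*

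**What the plan says.** Section 2.6 (Analysis methods) of the protocol article fixes the efficacy cohort: "The analysis cohort will be defined as patients who complete the implant defibrillation testing protocol". Section 2.2 (Data collection) runs testing at implant "until the sample size requirement of at least 95 completed defibrillation testing protocols has been reached". Section 2.3 instead asks for testing in at least the first 95 consecutive implanted patients.

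Section 1.3 defines success by two routes: "a single 18 Joule shock terminates an induced sustained shockable ventricular arrhythmia (SSVA) or if two consecutive induced SSVAs are terminated with 25 J" shocks. The Figure 2 caption and the Discussion repeat these two routes.

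The objective is met if the lower limit of the two-sided 95% credible interval exceeds 88%. Section 2.4 reports the design assumptions: "a defibrillation success rate of 97% was assumed to study statistical power" and "To assess the Type I error, a success rate of 88% was assumed". It concludes that at least 95 completers give power above 90% and a Type I error below 2.5%. The prior is a skeptical Beta whose parameters are left to the supplement.

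**The concern.** The two routes to success need different amounts of testing. A patient converted at 18 J has met the endpoint after one shock and cannot then be incomplete. A patient not converted at 18 J can succeed only through two consecutive conversions at 25 J, and the test may stop before that is settled. After a first shock, whether a patient stays in the cohort can therefore depend on the result of that shock. Replacing unfinished tests until 95 are complete refills the cohort without recording the loss.

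This is the only primary efficacy endpoint of a single-arm pivotal study, and it is judged against a fixed goal with little slack. The safety objective in the same section is handled differently: it includes every patient with an implant attempt.

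**Working it through.** **Inputs from the article.** n = 95, goal 88%, design success rate 97%, success if the 2.5% posterior quantile exceeds 0.88.

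**Assumptions.** A flat Beta(1,1) prior, because the Beta parameters are not in the article. Success at 18 J q = 80%. Patients stopped after an 18 J failure have the same chance of eventual 25 J success as other 18 J failures. The share of 18 J failures lost, d, is varied because no rate is given.

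**Step 1: reproduce the plan's figures.** With x successes in n, the posterior is Beta(x+1, n−x+1).
- x = 89 of 95: lower limit 86.9%, not met.
- x = 90 of 95: lower limit 88.3%, met. The pass mark is 90, so 5 failures are allowed.
- P(X ≥ 90 | 95, 0.88) = 2.28% and P(X ≥ 90 | 95, 0.97) = 93.3%.

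Both agree with the stated Type I error below 2.5% and power above 90%.

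**Step 2: effect of losing 18 J failures.** Let c be the chance that an 18 J failure would succeed at 25 J. At a true rate of 88%, c = (0.88 − 0.80)/0.20 = 0.40.

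Completer rate = [q + (1−q)(1−d)c] / [q + (1−q)(1−d)]

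| d | Lost, as share of all tested (0.20 × d) | Completer rate | P(X ≥ 90) |
|---|---|---|---|
| 0 | 0% | 88.0% | 2.3% |
| 5% | 1% | 0.876/0.99 = 88.5% | 3.1% |
| 10% | 2% | 0.872/0.98 = 89.0% | 4.2% |
| 20% | 4% | 0.864/0.96 = 90.0% | 7.8% |

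In 95 tested patients about 0.20 × 95 = 19 would fail at 18 J, so d = 5% is about one patient. Varying q from 70% to 85% gives 3.0% to 3.2% at d = 5% and 6.9% to 8.2% at d = 20%.

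**Step 3: sensitivity to the prior.** Some more skeptical priors, such as Beta(1,2) or Beta(2,2), move the pass mark to 91. The Type I error is then 0.8% with no loss, and 1.2%, 1.7% and 3.3% at d = 5%, 10% and 20%. Power at 97% would be 84.3%, which does not match the stated power above 90% at n = 95.

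**Step 4: at the design rate.** At a true 97%, c = (0.97 − 0.80)/0.20 = 0.85. With d = 10% the completer rate is 0.953/0.98 = 97.2%, a shift of 0.2 points.

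**Step 5: a borderline result.** Suppose stopped tests are added back as failures.
- 90/95 (88.3%, met) becomes 90/96 (87.0%, not met) with one stopped test.
- 91/95 survives one (88.4%) but not two (87.2%).
- 92/95 survives two (88.5%) but not three (87.3%).

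**Step 6: losses that do little harm.** Loss unrelated to shock outcome, for example in patients who cannot be induced, leaves the rate unchanged. Loss only after a first 25 J conversion shifted it by less than 0.2 points, in either direction, in the cases tried.

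**The case against.** The strongest reply is that the article never defines what completing the protocol means. A full protocol could say that a sequence stopped after a failed shock is complete and counts as a failure, and then no bias arises. Figure 2 is not shown, and details of the efficacy analysis are left to supplementary methods. This stands, and it makes the concern conditional. It does not remove it, because the completers-only cohort and the replacement of unfinished tests are stated rules, not omitted detail.

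A reader might infer that success *is* biased upward, that most incomplete tests are 18 J failures, and that the stated Type I error has already been lost. The documents do not support this. They do not say who fails to complete or how often. Patients with no inducible arrhythmia, or stopped before any shock, also start without completing and need not bias the result. The order of 18 J first and 25 J afterwards is itself inferred from the wording of the success criteria.

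Larger figures are also tempting. If only patients who would finally have failed are removed, dropping 10%, 25% or 50% of them at a true 88% gives a chance of passing of 4.5%, 11.5% or 43%. That model is one-sided, since an abandoned 18 J failure might still have succeeded at 25 J.

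Finally, failure scoring can overcorrect. At a true 97% with q = 80%, the scored success rate is 0.97 − 0.20 × d × 0.85. That is 96.15% at d = 5% and 95.3% at d = 10%, and the chance of 90 or more successes in 95 falls from 93% to about 84% and 71%. This stands as a real cost of the fix.

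**Conclusion.** The concern holds in conditional form. The cohort rule allows exclusion that depends on the outcome, and after a first shock that exclusion can fall only on patients without an 18 J success. If tests stopped after a failed shock are treated as incomplete, the success rate can be biased upward. Under the stated assumptions, losing about 1% of tested patients in this way already takes the Type I error past 2.5%, to 3.1%; losing 4% takes it to 7.8%. One such test can reverse a result at the pass mark.

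The size rests on a flat prior, an assumed 80% success at 18 J, stopping unrelated to the 25 J outcome, and a non-completion rate that the article does not give. For a lead performing at 97% the effect is small. The risk is that a lead at or near 88% passes.

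**What to change.** - Define the efficacy cohort as every patient with an induced arrhythmia and at least one protocol shock.
- Score a test stopped after a failed shock, with neither success criterion met, as a failure. Do this in the primary analysis, or at least in a pre-specified sensitivity analysis that must be reported beside the completer result.
- Report separately the patients who were not inducible and those stopped before any shock.
- Reconcile section 2.2 (95 completed protocols) with section 2.3 (first 95 consecutive implanted patients), so that it is clear which patients are counted and when the testing requirement is met.

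The cost is more than a change of wording. The reported success rate becomes less favourable. If failure scoring is primary, the power claim above 90% in section 2.4 must be restated to allow for stopped tests. Using it as a mandatory sensitivity analysis avoids restating power but leaves the primary result open to the bias.
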